# **Trial Protocol**

## **A randomized controlled trial of an acceptance and commitment therapy-based parenting program for improving parenting stress and other health outcomes of parents and children with autism**

### **1 Introduction**

#### **1.1 Definition, prevalence, and disease burden of children with autism**

Autism is a heterogeneous neurodevelopmental condition with a specific combination of persistent deficits in the ability to initiate/sustain reciprocal social communication and interaction, and by a range of repetitive, restrictive, and inflexible patterns of interests, behaviors, or activities. Autism affects approximately 1% of the population globally, one in 44 children aged below eight years in the United States, and 1.8 million (0.7%) of Chinese children aged 6 to 12. The presence of these autism-related conditions significantly affects their capacities for independent living, educational attainment, skill acquisition, and social integration, which leads to a propensity for long-term dependency and challenges for their parents and other family caregivers.

#### **1.2 Needs and challenges of parents of children with autism**

Parenting children with autism can be more stressful and challenging than parenting children with typical development. Due to the constraints in healthcare, educational, and social services, parents of children with autism are obligated to fulfil dual roles as caregivers (e.g., coping with their children's autism-related conditions and comorbidities) and as partners in complex and intensive interventions (e.g., parent-mediated interventions). As a result, these

parents had ongoing parenting stress and emotional turmoil (a set of negative and chronic emotional states such as guilt, grief, irritability, and pessimistic about the future) in managing their children's conditions/behaviors. These emotional problems reduce parents' ability to sustain daily roles and increase the potential for developing mental health problems. Cross-sectional studies for parents of children with autism reported that 34.2% of them had clinically significant depressive symptoms, 44% had anxiety symptoms, and 55% had psychological distress. These emotional and mental health problems have been found to be associated with inadequate self-care practice, inflexible parenting practices, and reduced parenting competency. These factors ultimately have a detrimental impact on their autism children's health outcomes. Furthermore, it is common for parents of children with autism to express doubts regarding their own ability to recognize and comprehend the needs of their children with autism, as well as manage children's conditions and challenging behaviors. For parents of children with autism, lower levels of parenting competency are associated with increased parenting stress and decreased motivation to participate in children's interventions.

Therefore, given the high prevalence of mental health problems and unmet needs (e.g., limited access to mental health services and ASD-related knowledge) among parents of children with autism, it is crucial to develop a supportive intervention that not only assists these parents in improving their mental health and well-being but also provides them with the necessary knowledge and abilities to effectively address the conditions and behaviors of their children with autism.

## **2 Literature review and research gaps**

## 2.1 Literature review on parental interventions

Traditional behavioural parent training, such as parent-mediated interventions, has been suggested to enhance the parental ability to manage children's conditions and behaviours, and promote parent-child interactions effectively. However, these interventions have faced criticism for their narrow focus on the outcomes of children with autism, often neglecting the psychological difficulties experienced by parents of children with autism. Consequently, an increasing number of parent-focused interventions have been developed to address this limitation and fulfil the needs of parents of children with autism. Parent-focused interventions primarily target parents' health outcomes such as mental health and well-being, and equip parents with knowledge and/or skills that enable them to effectively manage their psychological experiences and flexibly respond to their children's needs and conditions. Various approaches have been developed and implemented in parent-focused interventions for supporting the parents of children with autism, such as cognitive behavioural therapy (CBT, aiming to identify and modify irrational emotions, cognitions, and behaviours), mindfulness-based interventions (MBIs, which aim to promote an individual's capability to be present in the moment without judgment), Acceptance and commitment therapy (ACT), psychoeducation (aiming to empower individuals with knowledge and skills to better manage and cope with mental health or behavioural challenges), among others. However, the effectiveness of parent-focused intervention in improving mental health and well-being for parents of children with autism were inconsistent and inconclusive because different approaches and formats used,

increasing the heterogeneity of the study groups/interventions and being unable to estimate the pooled effects of individual intervention approaches.

## **2.2 Summary of a systematic review on parent-focused interventions**

Therefore, a systematic review and meta-analysis was conducted to evaluate the effectiveness of their parent-focused interventions on promoting parents' mental health (e.g., stress, depressive symptoms, anxiety, and parental distress) and well-being (e.g., subjective well-being and parent-child relationships), as well as ameliorating children's autism symptoms and emotional and behavioral problems (EBPs), when compared with active/inactive controls.

The systematic review identified a total of 21 RCTs using two-group, pretest-posttest design. The meta-analysis results showed that parent-focused interventions could reduce parents' stress (Hedge's  $g=-1.26$ ), depressive symptoms ( $g=-0.71$ ), and distress ( $g=-0.44$ ), and children's EBPs ( $g=-0.21$ ), and improved parent-child relationships ( $g=0.51$ ) post-intervention, when compared with active/inactive control groups, with moderate to high certainty of evidence. Moreover, ACT- and mindfulness-based intervention and parenting skills training were identified as the potential optimal intervention approaches to support autism parents' mental health and well-being in this systematic review and meta-analysis.

**ACT.** As a "third wave" of cognitive therapy, ACT composed of six interrelated processes/domains (acceptance, cognitive defusion, contact with the present moment, self-as-context, values, and committed action) and combines mindfulness principles with behavioral therapies to facilitate positive changes in psychopathology and behaviors in parallel with improving one's psychological flexibility. ACT seems especially applicable in addressing the

emotional and mental health problems experienced by parents in caring for their children with autism. The preliminary effectiveness of ACT-based interventions in providing support for parents of children with autism was found consistent among four included studies, including one randomized controlled trial (RCT) and three pilot-RCTs. All of them were conducted using a face-to-face group format at weekly intervals, involving parents only, having "some concerns" risk of bias and small sample sizes ( $N < 60$  per study). The findings showed potential benefits of ACT-based intervention on several aspects of parents' psychological problems (e.g., parenting stress, distress, and depressive symptoms; Hedges'  $g$  ranged from 0.41 to 5.81) and well-being (e.g., psychological flexibility, mindful awareness, cognitive fusion, and personal value;  $g$  ranged from 0.39 to 6.08) post-intervention, when compared with either no treatment, treatment-as-usual or parent training group.

**Parenting skills training.** A component analysis reported that integrating psychological intervention (e.g., mindfulness-based intervention) with behavioral parenting skills training showed more favorable effect size than the psychological intervention alone ( $g = -0.83$ ) and parenting skills training alone ( $g = -0.99$ ) on parenting stress for parents of children with autism^28. Parenting skills training targets parents' needs in acquiring autism-related knowledge, strategies and skills to enhance parent-child interaction and communication, and effective management of their children's conditions and behaviors. By integrating ACT with parenting skills training, parents' requirements for self-care and attending to their children's conditions and behaviors could be met. Additionally, this approach could mitigate the psychological

difficulties that parents face when caring for children with autism and enhance their awareness and sensitivity to identify their children's development changes and needs.

**Optimal intervention format.** Optimal characteristics of parent-focused interventions, including targeted participants (only involving parents instead of parent-child dyads), intervention duration (5-8 weeks with weekly intervals), and delivery mode (group-based), were identified from the systematic review to inform the design of an ACT-based parental training intervention for improving these parents' mental well-being and their autism children's behavioral health outcomes.

## **2.2 Research gaps of existing autism-based interventions for parents of children with autism**

First, only four experimental studies of ACT-based interventions for parents of children with autism were conducted. All of them were not high-quality RCT design (e.g., without allocation concealment and intervention adherence and pre-specified study protocol) and inadequate sample sizes and short follow-up periods (mainly pretest-posttest design); and they had inconsistent health outcomes (especially children's outcomes).

Second, the identified studies using ACT as the sole intervention approach focusing on parents' self-care but not caring for the parents' learning/training in caregiving needs and support for their children's development. As both parents' psychosocial health and their children's caring/behavioral needs are equally important, combining these two potential effective intervention approaches (ACT + parenting skills training) to be tested in a high-

quality RCT on both parents' and their autism children's psychosocial health outcomes is recommended.

Third, the ACT-based interventions were all performed by psychotherapists, such as psychologists and behavior analysts. When considering limited resources (e.g., time, cost, and staff) in parent-focused interventions, training non-specialist providers such as nurses and social workers to administer an ACT-based parenting program may be more feasible, applicable and even cost-effective in community care settings. For example, a parenting program developed by world health organization which training parents, nurses, and social works as primary care provider showed significantly improve on parental stress, competence, and parent support of interaction for Italian parents of children with ASD post-intervention and 3-month follow-up time points, as compared to the treatment-as-usual control group.

Fourth, the delivery mode of all four studies identified was conducted face-to-face, and the feasibility and effectiveness of blended (combine the face-to-face and online modalities) ACT for parents of children with autism is still unknown. According to a recent RCT , there were no significant differences found between online and in-person ACT interventions for parents of children with typical development in terms of their effect on parents' stress levels, psychological flexibility, emotional regulation skills, and satisfaction with life post-intervention. Indeed, online participation has several advantages, especially for parents of children with autism who need to balance multiple parenting roles. It eliminates time and space constraints, allows for better treatment adherence, and saves costs for both the service provider and parents. Likewise, face-to-face intervention allows direct observation and

identification of clinically relevant behaviors in therapy that help to contextualize and provide the client with the appropriate exercise or metaphor according to the clinical conversation. And based on a previous RCT, ACT-based parenting skills training with a blended modality (2-session ACT plus 9-session parenting skills training) significantly reduced psychological distress and improved psychological flexibility, confidence in managing behaviors, and family adjustment post-intervention for parents of children with acquired brain injury, compared with the care-as-usual group. Therefore, considering the advantages of these two modalities and the confirmed feasibility and efficacy of ACT-based parenting training with a blended modality for parents of children with other developmental disabilities in adjusting parents/family outcomes, future studies are recommended to explore the effectiveness of blended ACT for parents of children with autism.

Finally, all the ACT-based interventions were conducted in Western countries and thus the findings might not be transferable/generalizable to the Chinese context, where there are very limited practice guidelines, policies, and resources for autism family care.

Therefore, it is proposed to develop and validate an ACT-based parenting training program, to test the effectiveness of the validated intervention with a rigorous RCT design for improving both parents' and their autism children's psychosocial health outcomes in mainland China.

### **3 Theoretical framework: Model of stress in families of children with developmental disabilities**

The theoretical model of stress (Figure 1) in families of children with developmental disabilities, which was adopted by a pilot RCT of ACT-based program, has been used to

guide the intervention development. This model implied that the risk and protective factors, including personal resources, family system resources, informal social support, and formal supports in the model can moderate the relationships between stressors (related to children's characteristics and other life stressors) and parents' outcomes.

By applying the ACT-based parental training program, parents can address the unmet needs related to their personal well-being (e.g., emotional and stress management, self-care learning, and parenting skills training), family dynamics (e.g., parent-child relationship), and formal/informal support factors. After receive this program, parents would have better psychosocial adjustment and health outcomes such as lessening parenting stress and depressive and anxiety symptoms, and enhancing parents' psychological flexibility, parenting competency), as well as capability to successfully manage their children's illness and related problematic behaviors (e.g., children's emotional and behavioral problems; EBPs).

[figure not shown]

**Figure 1** Adapted model of stress in families of children with developmental disabilities (Perry, 2004) to explain distress symptoms in parents of a child with autism. ASD = Autism spectrum disorder.

#### **4 Operational definitions**

Operational definitions of the terminologies or variables used in this study are presented as follows:

**Children with autism.** In this study, this term refers to children aged 3–9 years who received a clinical diagnosis of autism according to DSM-5 diagnostic criteria. We do not reference prior affiliated diagnoses that are no longer recognized as separate entities in the DSM-5 (e.g., autistic disorder, Asperger’s disorder, pervasive developmental disorder—not otherwise specified, Rett syndrome, or childhood disintegrative disorder). If historical documentation or clinical reports use these legacy terms, they were treated as referring to autism under DSM-5 nosology and were verified against DSM-5–based diagnostic confirmation for eligibility. The 3–9-year period spans preschool and early primary school, a critical window for development in social interaction and communication, adaptive behavior, cognition, and emotion—domains closely linked to core ASD characteristics. Interventions during this period are particularly consequential for developmental outcomes. Moreover, children in these age stages often display more challenging behaviors than older age groups, which may contribute to elevated parenting stress.

**Primary family caregiver.** This term is operationally defined as the person who is living with their child with autism and takes the responsibility for coordinating caregiving activities,

consistently ensuring the provision of care and welfare for their children with autism, and typically dedicating the most time to fulfilling parental duties (at least four hours per day) .

## **5 Methods**

### **5.2.1 Study aim and objectives**

The aim of this study is to evaluate the effectiveness of ACT-based parenting program on parents' psychological health and their children's emotional and behavioural problems, when compared with usual-care-only.

The objectives of the main RCT are to assess the effects of ACT-based parenting program versus usual care on: a) parental outcomes: parenting stress (primary outcome), depressive symptoms, anxiety symptoms, psychological flexibility, and parenting competence; and b) children's outcome: emotional and behavior problems at immediately (T1) and six-month post-intervention (T2).

### **5.2.2 Research hypotheses for the main RCT**

Compared with a usual-care-only group, parents in the ACT-based parenting program in addition to usual-care-only will indicate significantly greater improvement in parenting stress (primary outcome), depressive symptoms, anxiety symptoms, psychological flexibility, and parenting competence, and their children's emotional and behavior problems at immediately, and six-month post-intervention.

### **5.2.3 Study design**

The main randomized controlled trial will employ a parallel-group, repeated-measures design and will adhere to the CONSORT (Consolidated Standards of Reporting Trials) guidelines .

#### **5.2.4 Settings and Subjects**

Parents will be recruited through seven rehabilitation institutions for children with developmental disabilities or delays in Guangdong Province, China. All seven institutions are located in urban districts of Shenzhen—a highly developed metropolitan area—and share comparable characteristics in organizational structure, funding support, service offerings, professional qualifications, and staff composition, representing services commonly provided by non-governmental institutions to children with ASD and their families in mainland China. Each institution is a privately operated, designated rehabilitation service provider authorized by the Shenzhen Disabled Persons' Federation and operates in accordance with government regulations. Under Shenzhen municipal policies for rehabilitation assistance for children with disabilities, intervention costs at these institutions can be subsidized by the government up to 50,000 RMB (approximately 7,021 USD) per child per year. The institutions included: Shenzhen Xinkangle Special Education and Rehabilitation Institution, Shenzhen Xingxinyuan Special Education and Rehabilitation Institution, Shenzhen Bougainvillea Special Needs Children's Rehabilitation Institution, Shenzhen Happy Nut Special Needs Children's Rehabilitation Institution, Shenzhen Love Ear Tree Special Needs Children's Rehabilitation Institution, Shenzhen Wishing Tree Special Needs Children's Rehabilitation Institution, and Shenzhen Stars Special Needs Children's Rehabilitation Institution. The first four sessions of

the intervention were administrated face-to-face at the children's rehabilitation institutions, and the last four sessions were conducted through an online videoconferencing platform (Tencent Meeting).

Participants (Parents) will be eligible if they are: (1) aged  $\geq 18$  years old; (2) parent of children aged between 3 to 9 years diagnosed with autism; (3) primary family caregivers responsible for daily care of their children with autism; (4) able to communicate and understand Mandarin; and (5) able to complete online sessions and questionnaires through mobile phone or computer.

Participants will be exclude if they had: (1) been diagnosed with clinically significant mental (e.g., anxiety disorders, depression, post-traumatic stress disorder, schizophrenia, developmental disorders) or medical conditions (e.g., spinal cord injury, spina bifida, cerebral palsy, multiple sclerosis, hearing/visual impairment) that prevented participation; (2) exhibited unstable or extreme intentions or behaviors (e.g., self-injury or suicide); (3) been caring for at least one other family member with an acute or chronic illness; (4) a planned or imminent hospitalization for their child with autism (including admission to an inpatient unit or long-term residential facility); and/or (5) been enrolled in another parent support intervention.

### **5.2.5 Sample size estimation**

The effect size of parenting stress (primary outcome) was used to calculate the sample size. Our systematic review and meta-analysis found that the effect sizes of ACT-based interventions on reducing parenting stress in parents of children with autism were large, that is, Hedges'  $g = -1.25$  ( $n=20$ ) in Marion et al. (2021) and  $d = -5.81$  ( $n=60$ ) in Çiçek & Öncel (2023)

 at immediately post-intervention when compared with parent training or treatment-as-usual control group, respectively. The pooled effect size of parent-focused interventions in parents of children with autism also demonstrated a large effect size (Hedges'  $g=-1.26$ ) on parenting stress immediately post-intervention, when compared with the active/inactive control groups. However, given very limited studies of ACT-based interventions and relatively small sample sizes used, a medium effect size of 0.5 (Cohen's  $d$ ) on parenting stress was adopted to conservatively estimate the effects of this newly developed ACT-based parenting program for the parents caring for an autism child. Furthermore, attrition in RCTs can lead to biased treatment effect estimates, reduced statistical power, and limited generalizability . To determine the appropriate sample size, the expected attrition rate must be considered. Five of the included studies in the systematic review and meta-analysis had similar follow-up duration as this main RCT. The attrition rates ranged from as low as 0%  to as high as 59.65%. Therefore, to mitigate the risk of decreased statistical power, an average attrition rate of 16.9% was considered for the main RCT. Finally, taking into account the possible attrition rate of 16.90%, a total of 154 participants (77 per study group) were required for a statistical power of 80% and statistical significance of 5%, two-tailed, using G\*Power v. 3.1.9.7.

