#### **5.2.7 Randomization and concealment**

Eligible participants will be randomly assigned in a 1:1 ratio to either an ACT-based parenting program plus usual care (intervention group) or usual care only (control group), using permuted block randomization with variable block sizes of four or six. The allocation sequence will be generated by an online randomization program and administered by a research assistant (a registered nurse with a master's degree in nursing) who will not be involved in participant recruitment, intervention delivery, or outcome assessment. Group allocation will be concealed from outcome assessors, rehabilitation school teachers, parents, and children using sequentially numbered, opaque, sealed envelopes.

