#### **5.2.8 Intervention Group**

In addition to usual care, parents in the intervention group will receive eight weekly sessions (2 hours per session) of an Acceptance and Commitment Therapy (ACT)-based parenting program delivered by the research team. The program will be administered in a

blended group format (face to face and online), with approximately 6–8 participants per group. The curriculum will cover four domains: (1) emotional and stress management (ACT); (2) autism-specific parenting skills; (3) autism-related education; and (4) self-care.

To establish rapport between the facilitator and participants, Session 1 will be delivered face to face. Sessions 2–4 will also be delivered face to face because they include experiential exercises (e.g., role-playing, mindfulness practices) that support learning of complex techniques and concepts. Sessions 5–8 will be delivered via an online videoconferencing platform (Tencent Meeting). During the final four online sessions, parenting practices will be taught step by step using instructional parenting videos, and core ACT principles (e.g., self-as-context) will be introduced using animated metaphor videos. All videos will be drawn from trustworthy, validated sources recommended by the World Health Organization’s Caregiver Skills Training for Families of Children with Developmental Delays and Disabilities (WHO-CST) and/or ACT manuals. Parents will receive a workbook outlining core ACT principles, key parenting skills, and weekly homework. Participants will be able to access online mindfulness practice videos after class by scanning QR codes provided in the workbook. A session-by-session outline of the ACT program will be provided in Table 1.

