#### **5.2.12 Data analysis**

Data analysis will be conducted in R software (Version 4.4.1 for Mac). Descriptive statistics will summarize sample characteristics and study outcomes. Assumptions of normality and homogeneity will be assessed when examining baseline group differences. Outcome analyses will use generalized estimating equations (GEE) under the intention-to-treat (ITT) principle to compare differential changes between groups across time points. All randomized participants will be retained in the models in accordance with ITT. Missing data will be handled within the GEE framework using robust standard errors, providing valid population-averaged estimates under Missing Completely at Random (MCAR) or Missing at Random (MAR) assumptions. When the proportion of missing data exceeds 10%, multiple imputation will be performed. If GEE results indicate significant effects, post hoc comparisons of estimated marginal means will be conducted to examine within-group and between-group differences for individual outcomes.

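### The sample size makes no allowance for therapy-group clustering in the intervention arm, and the analysis section does not name therapy group in the GEE

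*Protocol*

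**What the plan says.** Section 5.2.5 of the protocol bases the sample size on parenting stress. It takes "a medium effect size of 0.5" (Cohen's d) and 16.9% attrition, and concludes that "a total of 154 participants (77 per study group) were required for a statistical power of 80% and statistical significance of 5%, two-tailed". It mentions no intraclass correlation, group size or design effect.

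Section 5.2.7 has individual parents "randomly assigned in a 1:1 ratio". Section 5.2.8 then delivers the programme as eight weekly two-hour sessions in a "blended group format (face to face and online), with approximately 6–8 participants per group". Under section 5.2.9 control parents receive routine institutional services and are not formed into trial groups.

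Section 5.2.12 states: "Outcome analyses will use generalized estimating equations (GEE) under the intention-to-treat (ITT) principle to compare differential changes between groups across time points". It mentions robust standard errors only when dealing with missing data. It names neither the cluster unit nor the working correlation, and mentions neither therapy group nor institution.

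**The concern.** Intervention parents share a group for eight weeks, and interaction is part of the treatment. Section 5.2.8 describes role-play, and Table 1 lists peer relationships as an aim of the first session and group discussion in most sessions. Outcomes of parents in the same group may therefore be correlated, while control parents have no matching structure.

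A sample size that treats all parents as independent leaves this out. If the analysis also clusters on the parent alone, the sandwich variance captures correlation between one parent's repeated measurements but not between parents in one group. The variance of the intervention-arm mean is then understated. At stake on the primary outcome are a two-sided error above 5%, confidence intervals that are too narrow, and less than 80% power for a test that does hold its 5% level.

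**Working it through.** **1. Reproduce the stated figure.** Inputs from 5.2.5: d = 0.5 (SD = 1), two-sided 5%, power 80%, attrition 16.9%. A two-sample t-test (noncentral t) needs 64 per arm, with power 0.801. Inflating for attrition gives 128 / (1 − 0.169) = 128 / 0.831 = 154.03, that is, 154. The match is exact under independence. At 64 completers per arm the power is 80.1%, so nothing is held in reserve.

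**2. Set up the partially nested design.** 77 intervention parents in groups of 8 to 6 make 77/8 = 9.6 to 77/6 = 12.8, so about 10–13 groups. With a mid-range group of 7 and attrition spread evenly, completers per group are m = 7 × 0.831 = 5.8, and the number of groups at analysis is g = 64/5.8 = 11.0.

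The ICC is an assumption, because the protocol gives none: 0.01, 0.02, 0.05, 0.10. The design effect applies to the intervention arm only.

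- DE = 1 + (m − 1) × ICC
- Variances: v1 = DE/64 (intervention), v2 = 1/64 (control); true SE = √(v1 + v2)
- SE if groups are ignored: √(2/64) = 0.1768
- Type I error if groups are ignored: 2 × [1 − Φ(1.96 × 0.1768 / true SE)]
- Large-sample power: Φ(0.5 / true SE − 1.96)
- Small-sample power: noncentral t with Satterthwaite df = (v1 + v2)² / [v1²/(g − 1) + v2²/63]

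**3. Worked case, ICC 0.05.** DE = 1 + 4.8 × 0.05 = 1.24. True SE = √(2.24/64) = 0.1871, which is 1.058 times 0.1768. Type I error = 2 × [1 − Φ(1.96/1.058)] = 6.4%. Large-sample power = Φ(2.673 − 1.96) = Φ(0.713) = 76.2%. With df of about 30, power = 73.4%.

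**4. Results over the assumed range (5.8 completers per group).**

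| ICC (assumed) | DE | SE ratio | Type I, groups ignored | Power, large-sample | df | Power, small-sample df |
|---|---|---|---|---|---|---|
| 0.01 | 1.05 | 1.012 | 5.3% | 79.8% | 33 | 77.5% |
| 0.02 | 1.10 | 1.024 | 5.6% | 78.9% | 32 | 76.4% |
| 0.05 | 1.24 | 1.058 | 6.4% | 76.2% | 30 | 73.4% |
| 0.10 | 1.48 | 1.114 | 7.8% | 71.9% | 26 | 68.7% |

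If groups stay at 7, type I error at ICC 0.02 / 0.05 / 0.10 is 5.7 / 6.8 / 8.6%, and small-sample power is about 75 / 72 / 66%. A simulation with 64 per arm and 40,000 runs per setting gave type I errors for groups of 7 of 5.7 / 6.8 / 8.6%, in agreement.

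**5. What the power columns mean.** They refer to a test that accounts for groups. A test that ignores groups would still reject often: at ICC 0.05, Φ[(0.5 − 1.96 × 0.1768)/0.1871] = Φ(0.82) = 79%. It does so only because its error rate is 6.4% rather than 5%. Part of the small-sample loss comes from having few groups rather than from the ICC itself, which is why power is 77.5% even at ICC 0.01.

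**The case against.** A reader might infer that the GEE treats all parents as independent and that its standard errors are certainly too small. The protocol does not say so. Section 5.2.12 leaves the cluster unit open, and a statistical analysis plan that is not shown could cluster on therapy group. What stands is that therapy group is not named and that parent-level clustering is the usual reading. The sample-size basis is a separate matter, because 5.2.5 fixes it.

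A reader might also infer that the 80% power is certainly not delivered. That needs a positive ICC, and the documents give none. At 0.01 the type I error is 5.3% and large-sample power is within a point of 80%. Only the upper part of the assumed range is material.

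Some features could lower the relevant correlation:

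- Section 5.2.13 speaks of a single intervener under session-by-session supervision. If one person leads every group, differences between therapists add nothing. Section 5.2.8 attributes delivery to the research team, however, so this is not settled.
- Section 5.2.4 places the face-to-face sessions at the institutions. If groups form by institution, part of the within-group correlation is an institution effect shared with controls, and a one-arm design effect would overstate the problem.
- Usual care in 5.2.9 includes some group education, but this is available to both arms.

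These points bear on the size of the ICC. None shows that it is zero, and the protocol does not argue that it is negligible.

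Finally, one might expect adjustment for baseline to recover the power. The protocol gives no baseline correlation, and a plain comparison of change scores gains nothing at a correlation of 0.5. Nor would adjustment repair standard errors that ignore group.

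**Conclusion.** The point holds as an omission. The 154 rests on independence between parents, which the group delivery in one arm does not support, and nothing in 5.2.5 or 5.2.12 allows for the grouping. The harm is conditional. If the within-group ICC is positive and the GEE clusters on the parent only, the error rate exceeds 5% and a valid 5% test has less than 80% power.

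Over an assumed ICC of 0.01 to 0.10, the consequence runs from minor (type I error 5.3%, power about 77% with small-sample df) to material (7.8%, about 69%). These figures assume 64 completers per arm, about 5.8 per group, clustering in the intervention arm only, and no credit for baseline adjustment. Confidence is high about the omission and limited about its size. Severity: should-fix.

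**What to change.** - **Data collection:** record a therapy-group identifier for every intervention parent. Without it the grouping may not be recoverable later.
- **Section 5.2.12:** account for therapy group in the intervention arm. Use either a mixed model with a group random effect in that arm only, or GEE clustered on therapy group with each control parent a singleton. In both cases specify a small-sample correction, since there will be only about 10–13 groups.
- **Section 5.2.5:** state an assumed ICC and give power as a range computed with small-sample degrees of freedom, for example about 69–77% for ICC 0.10 to 0.01 at 5.8 completers per group. Do not quote the large-sample 72–80% alongside a small-sample analysis. Do not claim that baseline adjustment makes up the loss unless a baseline correlation is stated.

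The cost is some wording and one variable, with no extra recruitment. The downside is a less favourable stated power and slightly wider confidence intervals.
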